#### Secondary outcomes

The proportion of breastfeeding at discharge: Based on the record on CRF, we will calculate the number of infants who are exclusively breastfeeding without formula top-ups.The exclusive breastfeeding rate at 3 and 6 months after discharge: Breastfeeding status will continue for 3 or 6 months or until mixed feeding is established [40].Breastfeeding ability of preterm infants: The assessment of rooting, areolar grasp, duration of latching on, sucking, sucking burst, and swallowing [41]. It will be evaluated on discharge day. The Preterm Infant Breastfeeding Behavior Scale (PIBBS) will be used and the scale was developed by professionals and mothers of preterm infants [41].Length of hospital stays: Based on the record on CRF, we will calculate the duration of each subject from NICU admission to discharge.The number of complications: Based on the record on CRF, we will calculate the number of infants who have complications as follows:
♦ Intraventricular hemorrhage (IVH) diagnosed by cranial ultrasound [42]♦ Retinopathy of prematurity (ROP) diagnosed by funduscopic examination [43]♦ Bronchopulmonary dysplasia (BPD) defined by an oxygen requirement that persists beyond 36 weeks’ gestational age [44]♦ Necrotizing enterocolitis (NEC) diagnosed by identifying pneumatosis, intrahepatic portal venous gas, or free air by radiograph [45]♦ Sepsis diagnosed by blood culture [46]♦ Patent ductus arteriosus (PDA) diagnosed by cardiac ultrasound [47]Days requiring supplemental oxygen: Based on the record on CRF, we will calculate the days of oxygen therapy in any form for each subject.The degree of anxiety and depression in parents: In the Hospital Anxiety and Depression Scale anxiety subscale, A represents anxiety, while D represents depression, with each item divided into four grades. The total scores of anxiety and depression are obtained by superposition. A total score of 0–7 is normal, 8–10 indicates mild depression or anxiety, 11–14 indicates moderate depression or anxiety, and 15–21 indicates severe depression or anxiety [37].

### Sample size

Sample size calculation is performed based on the primary outcome that is the time to achieve full oral feeding. The average days to achieve full oral feeding was 14 days with a standard deviation of 7 days in the control group according to the previous study. The time for the intervention group to achieve full oral feeding was 4 days shorter than that of the control group [48]. The sample size of 66 in each group could achieve 90% power to detect a difference of 4.0 between the groups with estimated group standard deviations of 7.0 and with a significance level (alpha) of 0.05. At least 74 subjects will be recruited in each group considering a 10% drop rate. Sample size calculation was performed by Power Analysis & Sample Size ® software version 16.0 (NCSS, LLC. USA).

### Randomization

The subjects will be randomly allocated to the intervention group or the control group by block randomization method with a block size of 4 and allocation of 1:1. The randomization will be done by SAS version 9.4 (SAS Institute, Inc). A sequence of subjects’ IDs and intervention allocations will be generated, which by creating a random variable and ordering on that variable. The allocation sequence will be concealed by the statistician and placed in sequentially numbered, opaque, sealed, and stapled envelopes. After signing the informed consent from parents, the study investigators will open the envelopes in consecutive orders and randomly assign the subjects to the intervention group or the control group according to the allocation scheme in the envelope. The staff who analyze the outcome is unaware of the allocation of subjects.

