**Methods:**

This is a single-center, randomized controlled clinical trial conducted in the NICU and designed according to the SPIRIT Statement. The subjects included in the study are premature infants born between April 2020 and July 2021 with a gestational age of ≤30 weeks, birth weight of <1500 g, admission age of <72 h, and absence of congenital malformations. Those with oxygenation indices of >40 and those born to mothers with poor verbal communication skills will be excluded. A sample of 148 infants is needed. The infants will be randomized to the intervention (skin contact combined with mother’s breastfeeding model) or control group (routine pacifier sucking training model). The primary outcome is the time required to achieve full oral feeding. The secondary outcomes are the breastfeeding abilities of preterm infants as assessed by the Preterm Infant Breastfeeding Behavior Scale (PIBBS), breastfeeding rates at 3 and 6 months corrected gestational age, complication rates, duration of oxygen requirement, days of hospital stay, and satisfaction of parents.

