## Methods/design

### Study setting and design

We will conduct a randomized, open-label clinical trial in the NICU at the Children’s Hospital of Fudan University (CHFU) in Shanghai, China. CHFU has a capacity of 1000 beds with a large neonatal center consisting of 80 NICU beds. Patients requiring admission to the NICU are those who are especially critical, approximately 2200 annually. These patients are transported from all regions of the country, with a higher proportion from the Yangtze River Delta region. More than half of these patients are preterm with approximately 500 very low birth weight infants admitted to the CHFU annually. This protocol refers to the SPIRIT 2013 Statement (Standard Protocol Items: Recommendations for Interventional Trials). A SPIRIT checklist is seen in Additional file 1. The procedures of the trial are presented in Fig. 1.

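### One fixed block size of 4 in a single-centre, open-label trial lets an investigator who knows it foresee, in expectation, up to one third of allocations

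*Protocol article*

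**What the plan says.** The Randomization section specifies a "block randomization method with a block size of 4 and allocation of 1:1". The allocations are "placed in sequentially numbered, opaque, sealed, and stapled envelopes", and after parental consent "the study investigators will open the envelopes in consecutive orders and randomly assign the subjects to the intervention group or the control group". No stratification factor, second block size or central allocation is described. The only people said to be unaware of allocation are those who analyse the outcome.

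On setting, the abstract states "This is a single-center, randomized controlled clinical trial conducted in the NICU", and Study setting and design states "We will conduct a randomized, open-label clinical trial in the NICU". On size, the abstract states "A sample of 148 infants is needed".

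The Statistical analyses section plans a covariate-adjusted model for the primary outcome. It names gestational age, sex, birth weight, admission age and oxygenation index, and leaves the list open.

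**The concern.** Concealment has two parts. The next envelope must not be readable, and its content must not be deducible from those already opened. The envelopes deal with the first part. The second is weak here: there is one list and one small block size, and the investigators who open the envelopes learn every past assignment as they go.

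The envelope is opened only after consent, so steering would have to take place earlier, in deciding which family is approached and when. The protocol gives a possible motive. The intervention needs the mother in the unit for at least an hour each day, while infants are transported in from across the country. A mother who cannot provide skin contact or empty-breast sucking meets a dropout criterion. Someone who foresaw an intervention slot might therefore prefer a mother who can attend. The arms would then differ in ways that randomisation was meant to exclude, in an unmasked comparison of days to full oral feeding.

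**Working it through.** **Inputs.** Block size 4, ratio 1:1 (Randomization). Total 148 (abstract). 66 per group, difference 4 days, SD 7 days, 90% power, 10% dropout (Sample size). Two-sided 0.05 (Statistical analyses). Recruitment from 8 April 2020 to about 1 July 2021 (Trial status).

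**The plan's own figure.** The documents give no predictability figure, but the sample size reproduces. A two-sample t-test needs 65.33 per group, rounded up to 66 (power 0.903). Then 66 / 0.9 = 73.3, rounded up to 74, and 2 × 74 = 148. That is 148 / 4 = 37 complete blocks.

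**Allocations certain in advance.** A 1:1 block of 4 has 6 equally likely orders. An allocation is certain once one arm has used both its places in the block.
- Positions 1 and 2: never certain.
- Position 3: certain when the first two went to the same arm (AABB or BBAA), probability 2/6 = 1/3.
- Position 4: always certain.

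Expected number per block = 0 + 0 + 1/3 + 1 = 4/3. Share = (4/3) / 4 = 1/3. Over 37 blocks, 37 × 4/3 = 49.3 infants. The 95% range is 44 to 55, and the limits are 37 (one per block) and 74 (two per block).

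**Best guessing over all allocations.** The observer guesses the arm with more places left and tosses a coin when they are equal.
- Position 1: 1/2.
- Position 2: 2/3.
- Position 3: (1/3 × 1) + (2/3 × 1/2) = 2/3.
- Position 4: 1.

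Mean = (0.500 + 0.667 + 0.667 + 1) / 4 = 0.708.

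**How hard blocks are to follow.** The planned recruitment period is 449 days. 449 / 37 = about 12 days per block, which is easy to keep in mind.

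**Other block schemes.** The share certain is 25% for a fixed block of 6 and 20% for a fixed block of 8. For randomly varied sizes, a simulation of 148 infants assumed an observer who knows the possible sizes but not their order.

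| Scheme | Certain in advance | Best guess right |
|---|---|---|
| Fixed 4 | 33.3% | 70.8% |
| Varied 4, 6 | 5.6% | 69.2% |
| Varied 4, 6, 8 | 2.4% | 67.9% |

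Varying the sizes removes nearly all certainty but lowers the best guess only a little if the set of sizes is known. The sizes must therefore be withheld as well as varied.

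**What it could do to the result (assumption, not from the documents).** Suppose that only the certain allocations are steered, and that each is shifted by η days in prognosis: favourably for intervention slots, unfavourably for control slots. One third of each arm is affected, so the spurious difference is η/3 + η/3 = 2η/3. The standard error is 7 × √(2/66) = 1.22 days.

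| η (days) | Spurious difference (days) | Two-sided type I error |
|---|---|---|
| 0.5 | 0.33 | about 6% |
| 1.5 | 1.0 | about 13% |
| 2 | 1.33 | about 19% |

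The target difference is 4 days. The documents do not say what η would be, and it may be zero.

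**The case against.** The strongest reply is that the one-third figure is conditional. It describes an observer who knows the block size and follows every assignment. The article has the statistician conceal the sequence and does not say whether recruiting staff were told the block size. A condensed article may leave that to the full protocol. This stands, and it is why the figure is given as an upper scenario. The article also provides real safeguards: numbered, sealed envelopes, opened in order and only after consent. They limit tampering but do not stop deduction.

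A reader might go further in several ways that the documents do not support.
- That publishing the block size revealed it to recruiters. The article is dated 17 September 2021, after the planned end of recruitment around 1 July 2021. Any knowledge would have come from the investigators' own protocol.
- That the people who approach parents are those who open the envelopes. The Consent section names no role. The two may overlap, but this is not stated.
- That all ward staff see past assignments. In both arms the procedures begin only after mechanical ventilation is withdrawn, so for a ventilated infant the arm is not visible in care at first. The investigators who open envelopes do know it.
- That the list should have been stratified by gestational age. This is a preference: the primary model already adjusts for gestational age, and stratifying would not reduce predictability.
- That bias occurred. Nothing in the documents shows this.

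Adjustment is also a partial answer. Steering on measured severity, such as gestational age, birth weight or oxygenation index, would be corrected to some extent. Steering on maternal availability or motivation would not be, since no such covariate is named.

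**Conclusion.** The point holds as a design weakness that was cheap to avoid. With the stated scheme, a fully informed investigator could know in advance an expected one third of allocations (about 49 of 148, 95% range 44 to 55) and guess 70.8% correctly overall. This rests on two assumptions that the article neither confirms nor excludes: that someone able to influence enrolment knew the block size, and that this person tracked earlier allocations. One list at one site, with investigators opening the envelopes, makes the tracking easy. The figures measure how guessable the sequence is, not bias in days to full oral feeding. The size of any bias cannot be derived from the documents, and the sample size calculation is unaffected.

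**What to change.** **For infants still to be randomised.** Have the statistician generate the remaining list with randomly varying block sizes, for example 4, 6 and 8. Withhold the sizes, and the set they are drawn from, until enrolment ends from everyone who screens, obtains consent or opens envelopes. The Randomization section should say only that block sizes vary and are withheld.

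The cost is a change to the SAS code, new envelopes and slightly looser balance. The largest possible imbalance at any point rises from 2 (half a block of 4) to 4 (half a block of 8). A final split of 72 to 76 instead of 74 to 74 changes the variance factor from 2/74 = 0.02703 to 1/72 + 1/76 = 0.02705, which is negligible.

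**If enrolment has closed**, as the planned dates suggest:
- State who knew the block size during recruitment and what part they had in screening, consent and opening envelopes.
- From the envelope order, mark each allocation as predictable or not under blocks of 4, and compare baseline characteristics between the two sets, by arm. With about 49 predictable allocations, finding no difference would not exclude steering.
- Report the fixed block size as a limitation.

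This needs only data already held and a short addition to the report.

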### Data collection, management, analysis, auditing

Source of data acquisition:
The infants and the mother’s medical history will be obtained from the medical recordsInfants’ vital signs from the nursing information systemFeeding information and physical situation will be recorded in nursing documentsSkin contact and PIBBS will be assessed using real-time recordings of group membersInformation on correcting breastfeeding for gestational age of 3–6 months will be obtained from the mother’s telephone consultation

An electronic information collection form will be designed, and the team members will be responsible for recording all data on the paper of the day in the first instance.

The clinical research assistant is in charge of entering all the data in an electronic case report form (CRF). Another member of the research team verifies the newly entered data on paper every week. Another clinical research assistant checks the data of each case individually. The data can only be used after the completion of the study, with the data remaining anonymous prior to this. A clinical research assistant mandated by the sponsor will regularly supervise the study process every month. The elements to be audited during these visits will be defined prior to the start of the study. The results of each surveillance process need to be documented in writing, and epidemiological and statistical experts will be invited to work together to improve issues on a monthly basis. The database will be built using Access 2013 (Microsoft office Professional 2016); double data entry and check will be performed by the trained data entry staff.

### Statistical analyses

All analyses will be performed using SPSS 22.0 (IBM SPSS Statistics, IBM Corporation, Chicago, IL). The two-tailed significance level will be set to *P* < 0.05. An intention-to-treat (ITT) analysis will be used for the outcomes. For primary outcome analyses, the generalized linear model (GLM) will be used to test the difference of the time to achieve full oral feeding (days) between the groups, and the estimated means and two-sided 95% confidence intervals (CI) will be derived. The clinical factors including gestational age, sex, birth weight, admission age, oxygenation indices (OI), etc. will be adjusted in the covariate-adjusted analysis of the primary outcome by the GLM model. If any subjects dropped off from the primary endpoint, modified ITT analysis will be performed by using the available subjects.

All secondary outcomes will be analyzed by GLM. Binary secondary outcomes will be summarized as absolute numbers and percentages, and the difference and its 95% CIs between the two groups will be estimated. The continuous outcome will be presented as means and standard deviations (SD) and be analyzed with the same strategy and method with that is used for the primary outcome.

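### Infants who die or cannot be fed orally leave the primary analysis as dropouts, so mean days are compared only among achievers; this can bias the result in either direction and hides failures by arm

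*Protocol article*

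**What the plan says.** **Outcome.** The Protocol article (Primary outcome) counts days from first oral feeding to full oral feeding. Full oral feeding needs a share of the required volume by mouth, a period without gavage, and a rate of weight gain. An infant who never meets this definition has no value.

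**Dropouts.** Study subjects and recruitment lists three dropout criteria: death or withdrawal of treatment in hospital; a mother who cannot give skin contact or empty-breast sucking; and an infant who cannot be fed orally because of disease.

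**Analysis.** Statistical analyses names intention-to-treat and says that "the generalized linear model (GLM) will be used to test the difference of the time to achieve full oral feeding (days) between the groups". It adds that if subjects drop off from the primary endpoint, a modified intention-to-treat analysis uses those available. Continuous secondary outcomes follow the same method.

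**Secondary outcomes.** For length of stay, "we will calculate the duration of each subject from NICU admission to discharge". Oxygen days are counted per subject. Neither has a rule for infants who die. Six complications are listed; death is not among them and is not an outcome elsewhere.

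**Sample size.** "The sample size of 66 in each group could achieve 90% power to detect a difference of 4.0 between the groups". The SD is assumed to be 7.0 days in both arms, and recruitment is raised to 74 per arm to allow for 10% dropout.

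**The concern.** Whether an infant reaches full oral feeding is decided after randomisation, and it is what the intervention is meant to change. Comparing mean days only among those who get there gives up the protection of randomisation. If one arm loses more of its slow feeders to death, withdrawal of treatment or disease, that arm's remaining mean falls and it looks faster. If the other arm loses more, a real benefit is understated.

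The maternal dropout criterion makes unequal removal more plausible. It concerns delivery of skin contact and empty-breast sucking, so in practice it can fall mainly on the intervention arm. It also removes infants who may have a perfectly good primary value.

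The second problem needs no bias. In infants of 30 weeks or less, death and failure to feed matter more than a few days' delay, yet the primary result would not show them.

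**Working it through.** **1. The plan's own figure.** Inputs from Sample size and Statistical analyses: difference 4.0 days, SD 7.0, power 90%, alpha 0.05 two-sided.

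- Normal approximation: n = 2(1.960 + 1.282)² × 7²/4² = 2 × 10.51 × 3.0625 = 64.4, so 65 per arm.
- Two-sample t-test: n = 65.3, so 66 per arm; power at 66 is 90.3%.
- Dropout: 66/(1 − 0.10) = 73.3, so 74 per arm, 148 in total.

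The stated 66 and 74 reproduce. The sample size is not at fault.

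**2. No true effect on feeding time.** 74 per arm; gamma times with mean 14 and SD 7 in both arms ("The average days to achieve full oral feeding was 14 days with a standard deviation of 7 days in the control group"), so shape (14/7)² = 4 and scale 14/4 = 3.5. Failures are removed as planned and the rest compared by t-test, which is the unadjusted two-group GLM. Failure of 5% control v 15% intervention is an assumption, because the protocol gives no rates.

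| Who fails | Difference in means (days) | Intervention wrongly declared faster (nominal 2.5%) | Over repeat runs of 3,000 to 8,000 trials |
|---|---|---|---|
| Unrelated to speed | about 0 | about 2.4% | 2.2 to 2.7% |
| Risk proportional to underlying time | −0.4 | about 4% | 4 to 6% |
| The slowest infants | −1.3 | about 32% | 31 to 34% |

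Other assumed rates, slowest infants failing: 5% v 10% gives −0.7 day and 17%; 5% v 20% gives −1.8 days and 51%. With a proportional link the same rates give −0.2 day and 4%, and −0.7 day and 9%.

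**3. The same scenarios with failures ranked worst.** All 148 infants are kept, failures are ranked below every observed time, and a Mann-Whitney test is used. In every scenario with more failures in the intervention arm, that arm was declared better in at most 2.0% of trials.

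**4. Opposite direction.** With the design effect (10 v 14 days) and the slowest failing in 15% of control and 5% of intervention infants, the planned difference shrinks from −4 to −2.8 days and power falls to about 79%.

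**5. Power cost of the change.** At the design effect with 10% failure in each arm, ranked v planned: about 88% v 90% if failure is random, 97% v 97% if the slowest fail.

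**The case against.** **The bias is conditional.** It needs failure that is both unequal between arms and linked to slow feeding. Without the link the achiever mean is unbiased, as the first row of the table shows. The only rate in the protocol is a 10% overall dropout allowance, and 5% v 15% is a large imbalance. The Background cites lower infection severity with skin contact, which would point to fewer failures in the intervention arm. All of this stands, so the size is a range that includes nil and the direction is not known in advance.

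**A stronger figure is tempting.** Simulate a true 4-day benefit among achievers with random 5% v 15% failure: the planned analysis declares benefit in about 89% of trials and the ranked analysis in about 53%. A reader might take 89% as a false-positive rate. It is not. The difference is unbiased at −4.0 days in that setting, and the two tests answer different questions.

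**Stay and oxygen days.** A reader might infer that early deaths will count as short stays. The documents do not say so. Deaths are dropouts, stay ends at discharge, and the primary method carries over, so the natural reading is that deaths are left out. What stands is that neither reading shows the deaths.

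**Who is named as a dropout.** The criteria cover infants who cannot be fed orally because of disease, not those who start and never complete. The latter have no primary value and leave the available-subject analysis anyway. They may be few, since the Background gives full oral feeding as one of the discharge criteria.

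**The clock.** Time starts at first oral feeding, so an infant who dies earlier never enters it. This is a fair objection to simply adding a time-to-event analysis, and the fix must deal with it.

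**Detail left to an analysis plan.** This does not answer the main point: the article states the rule for the primary endpoint, and that rule is what can mislead.

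**Conclusion.** The point holds for the primary outcome. The protocol removes infants who die, have treatment withdrawn or cannot be fed orally, and compares mean days among the rest under a modified intention-to-treat label.

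Under no true effect and an assumed 5% v 15% failure, the chance of a false claim that the intervention is faster runs from about 2.4% to about 32%, against 2.5% nominal. Where it falls depends on how closely failure tracks slow feeding, which the documents do not settle. With the imbalance reversed, a real benefit is understated.

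Whatever the bias, an excess of deaths or failures in one arm would not appear in the headline, and death is not a listed outcome. For stay and oxygen days the conclusion goes no further than this: the handling of deaths is unstated and should be made visible. The change should be made before unblinded analysis.

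**What to change.** 1. Keep every randomised infant in the primary comparison, including those now dropped because the mother could not give skin contact or empty-breast sucking. Rank death worst and survivors without full oral feeding by discharge next, including infants who never start oral feeding. Achievers keep their time from first to full oral feeding as now defined. Compare the arms with a rank-based test.
2. Report the GLM mean difference in achievers as supportive, labelled as conditional on reaching full oral feeding.
3. If cumulative incidence of full oral feeding with death as a competing event is added, count it from randomisation, so that infants who die before their first oral feed are included.
4. Report in-hospital death and non-achievement by arm.
5. State that length of stay and oxygen days are shown with deaths identified, not counted as short durations.

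**Cost.** Changes to the analysis and outcome wording. No new data are needed beyond deaths and feeding status, which the trial already records. The headline becomes a rank-based contrast instead of a mean in days, which is harder to explain clinically; the supportive mean difference meets part of that need. Power is nearly unchanged in the settings simulated.

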## Background

Oral feeding is a complex sensory motor process which is affected by many factors. The brain of the preterm infant is not fully developed and thus neural development is incomplete. Oral feeding is difficult due to decreased abilities in sucking and swallowing, discordant breathing, and immature behavior state organizational capabilities [1, 2]. Studies report that 80% of preterm infants experience oral feeding difficulties with the degree of feeding difficulty related to gestational age [3, 4]. Although sucking and swallowing appears at 28 weeks of gestation, full coordination of sucking, swallowing, and breathing should be achieved at between 32 and 34 weeks’ gestation, which means that preterm infants less than 32 weeks of gestation are unable to feed orally by breast or bottle [4–9].

During neonatal intensive care unit (NICU) admission, preterm infants often require nasogastric or orogastric tube feeding before progressing to oral feeds once they are mature enough to do so [10]. Preterm infants’ readiness for full oral feeding is related to gestational age. According to research data on preterm infants at different gestational ages, full oral feeding was achieved at 10–36 days of life [11–14]. Establishment of full oral feeding in preterm infants is an important factor affecting the length of hospital stay and is also one of the criteria considered for discharge from the NICU [15–18].

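### Two generalized linear models are planned for the primary outcome at one 5% level, neither is named as deciding, and the covariate list of the adjusted one is open

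*Protocol article*

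**What the plan says.** The protocol article's Statistical analyses section gives the primary analysis in two steps. First, "the generalized linear model (GLM) will be used to test the difference of the time to achieve full oral feeding (days) between the groups", with estimated means and 95% confidence intervals; this sentence names no covariates. Second, for the same outcome and again by GLM: "The clinical factors including gestational age, sex, birth weight, admission age, oxygenation indices (OI), etc. will be adjusted in the covariate-adjusted analysis". One significance level, P < 0.05, is given for everything ("The two-tailed significance level will be set to"). Neither model is called primary, supportive or sensitivity, and no rule says what *etc.* may add. Continuous secondary outcomes follow the same strategy as the primary outcome.

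Three other places bear on this:

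- Sample size: "The sample size of 66 in each group could achieve 90% power to detect a difference of 4.0 between the groups". The calculation assumes an SD of 7.0 in each arm and alpha 0.05; it is a plain comparison of two means with no covariate term.
- Randomization: "block randomization method with a block size of 4 and allocation of 1:1", with no stratification factor stated.
- Background: preterm infants' "readiness for full oral feeding is related to gestational age".

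**The concern.** A confirmatory trial needs one model, fixed in advance, that gives the primary answer. Here two models estimate the same effect and each yields its own p-value at 5%. The text does not rank them, and the second can grow by whatever covariates *etc.* is taken to cover. When the two disagree, nothing in the article says which result stands, so the choice could be made after the data are seen.

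There is also a cost if the unadjusted model is meant to decide. The authors regard gestational age as prognostic and already plan to adjust for it and four other baseline factors, yet the deciding test would not use them. With no stratification stated, the adjusted model is also the only place where a chance imbalance in gestational age is allowed for.

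**Working it through.** **Inputs.** From the Sample size section: control mean 14 days, SD 7 in both groups, difference 4.0 days, alpha 0.05, 90% power, 66 per group, 10% dropout. The Statistical analyses section gives the two-sided level. The documents give no R² for the baseline covariates against the primary outcome, so R² is an assumption, shown over a range.

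**1. Reproduce the stated sample size without covariates.**

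- Normal approximation: n = 2 × 7² × (1.960 + 1.282)² / 4² = 64.4, so 65 per group.
- Noncentral t: SE = 7 × √(2/66) = 1.2185 and noncentrality = 4 / 1.2185 = 3.283 on 130 df, giving power 0.9029. At 65 per group power is 0.8985. The smallest n reaching 90% is therefore 66, as stated.
- Dropout: 66 / 0.90 = 73.3, so 74, as stated.

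The stated 90% power is therefore met by an unadjusted comparison of means.

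**2. Gain from adjustment.** Residual SD = 7 × √(1 − R²). Power is by noncentral t at 66 per group; half-width = 1.96 × residual SD × √(2/66).

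| Assumed R² | Residual SD | Power for 4 days | 95% CI half-width (days) |
|---|---|---|---|
| 0 | 7.00 | 90.3% | 2.39 |
| 0.05 | 6.82 | 91.7% | 2.33 |
| 0.10 | 6.64 | 93.0% | 2.27 |
| 0.20 | 6.26 | 95.4% | 2.14 |
| 0.30 | 5.86 | 97.3% | 2.00 |

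Five covariates cut the residual df from 130 to 125. With 125 df, power moves by 0.02 percentage points or less in every row, so the lost degrees of freedom are negligible.

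**3. Type I error if either model may be claimed.** Under the null, the two test statistics are approximately bivariate normal with correlation √(1 − R²). The chance that at least one exceeds 1.96 in absolute value is 1 − P(|Z₁| < 1.96 and |Z₂| < 1.96).

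| Assumed R² | Correlation | Either test significant | Simulation |
|---|---|---|---|
| 0.10 | 0.949 | 6.5% | 6.8% |
| 0.20 | 0.894 | 7.1% | 7.3% |
| 0.30 | 0.837 | 7.6% | 7.9% |

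The simulation column comes from 10,000 null trials per row, 66 per arm, comparing group alone with group plus five covariates. Each model used alone stayed near 5% (4.9% to 5.3% in these rows). The excess therefore comes from having a choice, not from either model. Neither column counts the further choice that *etc.* allows.

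**The case against.** The strongest defence is that the text can be read as ordered. The GLM without covariates comes first and is the one said to test the difference, and the sample size is an unadjusted two-mean calculation that reproduces exactly. An unadjusted primary test with an adjusted supporting analysis is a legitimate design. On that reading there is one deciding answer, and preferring the adjusted model is a matter of efficiency. Part of this stands: the unadjusted model is the likelier intention. But the article never says so and never calls the adjusted analysis supportive. A reader might infer that the unadjusted GLM is the declared primary test; the documents do not support stating that as fact.

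A second defence is that a journal article leaves covariate lists and model labels to a fuller document. That would answer silence. Here the article does state the analysis and its covariates, in an unranked and open-ended form.

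Third, the precision gain may be small. The Background statement concerns readiness for full oral feeding, whereas the primary outcome runs from first to full oral feeding. Entry is limited to 30 weeks or less, and in the intervention group bottle attempts start at 32 weeks, so the clock may start at a similar maturity whatever the gestation at birth. Gestational age and birth weight probably overlap. All of this stands, and it is why the range starts at R² 0.05, where the gain is about 1.4 power points. The overlap does not bias the group comparison.

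Fourth, the 6.5% to 7.6% applies only if success may be claimed on either model, which the article does not say. That is also right: the figure shows what the wording permits, not what is planned.

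Finally, complete OI data cannot be assumed. OI needs mean airway pressure and PaO₂, and nothing shows that both exist for every infant. The fix has to deal with this.

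**Conclusion.** The point holds in a limited form. The primary outcome has two planned GLM analyses at one two-sided 5% level, no statement of which decides, and an open covariate list. If either could be claimed, the type I error would be about 6.5% to 7.6% for assumed R² of 0.1 to 0.3, before any effect of *etc.* If the unadjusted model decides, the cost is efficiency: for assumed R² of 0.05 to 0.30, about 1 to 7 power points and a half-width that could have been about 0.06 to 0.39 days shorter (2.39 − 2.33 and 2.39 − 2.00).

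Three stronger readings are not supported:

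- That the trial is underpowered: the stated 90% is met without adjustment.
- That gestational age is known to bring a sizeable gain: no R² is given, and it could be small.
- That chance imbalance goes unaddressed or invalidates the unadjusted test: an adjusted analysis is planned, and under randomisation the unadjusted test keeps its 5% level.

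The calculations assume approximately normal residuals, a common SD of 7, and 66 evaluable infants per arm.

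**What to change.** Before the data are analysed, amend the Statistical analyses section as follows:

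- Name one primary analysis: the GLM with study group plus gestational age, birth weight, sex, admission age and admission OI, all taken before randomisation.
- Delete *etc.*, so that the list is closed.
- Label the comparison without covariates as supportive, to be reported alongside but not used to decide.
- State that infants with a missing baseline covariate, most plausibly OI, stay in the model through simple baseline imputation, so that adjustment does not remove randomised infants.

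Continuous secondary outcomes need no separate change, because they already follow the primary strategy. The sample size can stand: 66 per arm is enough without adjustment, and any gain from the covariates is a margin.

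The cost is a change of wording to a model already planned with these five covariates, five degrees of freedom out of 130, and a rule for missing OI.
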